### Interventions

The compression treatment and application of dressings will be performed in accordance with the standard procedure and the criteria of the nursing staff responsible. A priori, one treatment session per week is planned, but this may be modified in the light of the patient's response. Follow up of the patients recruited into this study will be continued for one year after the randomization process. The acupuncture sessions in Group A will be given at the same time as the cleansing of the ulcer and the changing of the compression bandage, and will continue for 3 months, or until the ulcer has healed completely (whichever occurs first). If, after these 3 months, the ulcer has not healed, the sessions will be continued (as before, together with the cleansing of the ulcer) for another 3 months. The acupuncture treatment will not be continued for longer than 6 months (figure 1).

**Figure 1 F1:**
[figure not shown]
**Flow diagram for the study**. Flow diagram for the diverse phases of the study.

The patients taking part in the study will be given recommendations about suitable hygiene-posture routines (resting with the legs raised, not standing for long periods, taking regular walks, keeping the skin well hydrated) and nutritional advice, if necessary. Both the compression treatment and the application of dressings will continue until the ulcer has completely healed. If a recurrence occurs before the one-year follow-up period has ended, the patient will be entered into a sub-cohort and given a new treatment plan.

#### Compression therapy (Groups A, B and C in the study)

Compression therapy will be given to all the participants in the study. Once the patient has been examined and the ankle/arm index calculated by means of a Doppler scan, an evaluation will be made of the state of the skin and of the shape of the leg, after confirming the absence of neuropathology, arterial pathology and cardiac insufficiency. The bandaging will be of a Class 3, high-compression multilayer type [42], following cleansing and application of the dressing, as follows: 1) With a 50% overlap, apply a cotton bandage in a spiral pattern from the base of the toes to just below the knee, without imposing any tension; 2) Apply an elastic bandage in a spiral pattern, with 50% overlap and stretched to 50% of its extension, from the base of the toes to just below the knee; 3) Apply a cohesive elastic bandage, with 50% overlap and stretched to 50% of its extension, from the base of the toes to just below the knee, and apply light pressure to ensure the adherence of the bandage. The oedema of the leg should be reduced by raising the limb for 15 minutes before applying compression.

#### Treatment of the ulcer for the patients given low-adherence, simple dressings (Study groups A and C)

▪ Cleaning: with tap water and mild soap [43-45], followed by careful drying

▪ Debridement: if necrotic tissue or sloughing are observed, perform enzymatic debridement, which may be combined with excision debridement, if necessary

▪ Managing infection: if infection is suspected, take a sample and begin treatment with silver sulfadiazine for a maximum of 2 weeks. If a culture study confirms the infection, treat using oral antibiotics

▪ Dressings: simple, low-adherence type (paraffin-impregnated tulle gras)

Any adverse reaction or side effect that may occur should be recorded in the Data Record (DR), with a detailed description and the date of occurrence.

#### Treatment of the ulcer for the patients given special dressings (Study group B)

▪ Cleaning: with tap water and mild soap, followed by careful drying

▪ Debridement: if necrotic tissue or sloughing are observed, perform enzymatic debridement, which may be combined with hydrogel to favour autolysis. If necessary, excision debridement should be applied

▪ Managing infection: if infection is suspected, take a sample and begin treatment with silver dressings (hydrofibre or hydropolymer) for a maximum of 2 weeks. If a culture study confirms the infection, treat using oral antibiotics

▪ Dressings: Cover with hydropolymers. Use alginate or hydrofibre dressings if exudate must be controlled

Any adverse reaction or side effect that may occur should be recorded in the DR, with a detailed description and the date of occurrence.

#### Acupuncture (Study Group A)

The nursing staff will be trained in the specific techniques of localization, puncture and manipulation in order to apply acupuncture at the perilesional zone of the ulcer(s), in healthy skin, using 4–8 needles, and at 2 points located on either side of the tibial crest of the affected limb (*Yinlingquan *SP9 and *Zusanli *ST36). The puncture will be carried out after cleansing of the ulcer. The needle to be inserted is a sterile, single-use filiform acupuncture needle, 30 mm long and 0.30 mm in diameter, fitted with a guide tube (S-J3030, manufactured by Seirin Corporation). Application will be made at each of the above-mentioned points, after sterilizing the skin, and with the patient lying face up or sideways. The puncture will be made vertically, unless otherwise specified, to a depth of 10–28 mm. The insertion will be followed by broad bidirectional rotational movements of the needle handle in order to produce the sensation of *Deqi*, commonly described as an irradiated feeling. The needle will be held in place for 20 minutes, and moved for 10 seconds every 5 minutes (4 manipulations per session). The acupuncture sessions will be applied for the first 3 months of this treatment programme or until the ulcer has completely healed. If complete healing is not achieved in this period, the sessions may be prolonged for another 3 months, after which the acupuncture treatment will be discontinued.

For each session, the number of needles used and the exact location of their application will be recorded. Any adverse reaction or side effect arising from this treatment should be recorded in the DR, with a detailed description and the date of occurrence.

A priori, the ulcer should be cleansed once weekly, the same frequency as the sensory stimulation with acupuncture. Nevertheless, this may be increased or decreased, at the discretion of the nursing staff.

All treatment will be given by the professional healthcare staff (nurses) employed at the Primary Healthcare Clinics, coordinated by the treatment programme head in each case. In order to standardize criteria and training procedures in the use of compression bandages, the data record system and the application of the study treatments, a **specific ad-hoc training course **will be given to all the healthcare staff involved in the study. This training will be structured as follows:

▪ Aims: acquisition of skills in applying acupuncture protocols for venous ulcers, in applying treatment techniques using the different kinds of dressing and in using the data record system. Standardization of criteria for applying compression bandages.

▪ Content: differential diagnosis of leg ulcers, calculation of the ankle/arm index, selection and localization of acupuncture points, the insertion of needles, the preparation and application of ulcer cleansing treatment, the reaction to possible infection, training in techniques with compression bandages, giving instructions to patients, implementing follow up, and giving all the study participants hygiene, posture and nutrition recommendations

▪ Instruction method: workshop

▪ Duration: 10 teaching hours

### Outcome measures

#### Primary outcome

##### Time until complete healing is achieved

Complete healing is defined as the complete epithelialization of all the leg venous ulcers, not just the reference one.

#### Secondary outcome variables

##### Complete healing at 3 months after beginning treatment

Complete healing is defined as the complete epithelialization of all the leg venous ulcers, not just the reference one (table 1).

**Table 1 T1:** Outcome measures. Work scheme with description of assessment visits and times.

	**Baseline (T0)**	**Weekly treatment**	**Evaluation at 3 months (T1)**	**Weekly treatment (if necessary)**	**Evaluation at 6 months (T2)**	**Evaluation at 12 months (T3)**
Sociodemographic data	X					
Ankle/arm index	X					
Nutritional study	X					
Localization of ulcer(s)	X		X		X	X
Area of main ulcer	X	X	X	X	X	X
Duration of the main ulcer	X					
Exudate culture (if necessary)	X	X	X	X	X	X
Changes in the size of the main ulcer		X	X	X	X	X
Characteristics of the main ulcer	X	X	X	X	X	X
Complete healing (date)		X	X	X	X	X
Pain intensity		X	X	X	X	X
SF-12	X		X		X	X
Adverse events/effects		X	X	X	X	X
Compliance with hygiene-posture recommendations	X		X		X	X
Location of treatment (clinic/home)		X		X		
Time employed in treatment		X		X		
Materials employed in treatment		X		X		
Number of needles used(Group A)		X		X		
Obtention of Deqi (Group A)		X		X		

##### Changes in the size of the surface area of the ulcer (in cm^2^)

When the baseline evaluation is made, the ulcer will be measured; if there are more than one, the largest ("the main ulcer") will be assessed. Nevertheless, the outcome variable of complete healing will be determined on the basis of all the ulcers observed on the patient when the baseline assessment is made. The area of the ulcer will be calculated using a compact digital tablet (Visitrak), with which the area can be assessed quickly, conveniently and accurately. The outline of the ulcer is drawn on a tracing sheet used as the digital screen; this has three layers to minimize the risk of cross contamination or secondary infection, and the layer in contact with the patient is sterile. The surface on which the data are recorded is kept clean and may be included in the patient's case history.

##### Pain intensity measured on a visual analogue scale

There exists sufficient evidence to corroborate the validity of the visual analogue scale of pain intensity. Many studies have demonstrated the validity of the concept [46] and its reliability [47,48]. With this method, the subjective intensity of pain may be measured quickly and straightforwardly. The patient is asked to mark the degree of pain intensity on a millimetric scale, from 0 (no pain) to 100 (the worst pain imaginable).

**Changes in the health-related quality of life **at 3, 6 and 12 months (12-item Short Form health survey, version 2) [49].

##### Adverse events – Adverse effects

A record will be kept of any adverse events or adverse effect observed by healthcare staff or reported by the patient or by his/her carer.

##### Cost-utility

Health utility will be measured in terms of the quality-adjusted life years (QALY) gained for each patient, calculated from the area beneath the SF-12 curve at 3 months from the start of treatment.

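### The QALY is stopped at 3 months although SF-12, treatment and resource recording all continue beyond it, so the cost-utility result misses later effects or mixes time periods

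*Protocol article*

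**What the plan says.** The Cost-utility paragraph, under the secondary outcomes, states: "Health utility will be measured in terms of the quality-adjusted life years (QALY) gained for each patient", and continues that this is "calculated from the area beneath the SF-12 curve at 3 months from the start of treatment". I read this as the area from baseline to the 3-month visit.

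Other parts of the protocol article bear on that horizon:

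- **Quality of life.** The outcome following the pain scale is change in health-related quality of life "at 3, 6 and 12 months", measured with the "12-item Short Form health survey, version 2". Table 1 marks the SF-12 at T0, T1, T2 and T3.
- **Follow-up.** Interventions says that follow-up "will be continued for one year after the randomization process".
- **Acupuncture.** The same section gives the upper limit: "The acupuncture treatment will not be continued for longer than 6 months".
- **Compression and dressings.** The text below Figure 1 says: "Both the compression treatment and the application of dressings will continue until the ulcer has completely healed". A patient whose ulcer recurs within the year receives a new treatment plan.
- **Resource use.** Table 1 records treatment time and materials in the second block of weekly treatment, after T1, as well as in the first.
- **Costs.** Research aims and questions asks for the total cost of each treatment without a 3-month limit. Data analysis lists the economic analyses but gives no horizon for any of them.

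Nothing in the article extends the QALY beyond 3 months, and nothing confines costs to 3 months.

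**The concern.** A cost-utility comparison needs costs and QALYs over one common period, long enough to take in the main differences between arms. Here the QALY stops at 3 months by an explicit rule, while treatment, its resource use, recurrence and the SF-12 itself all go on.

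Two outcomes are possible, and neither is satisfactory. If costs are also cut at 3 months, the analysis discards later treatment, later benefit and recurrence, although the data are collected. If costs run on, they are set against health gain from a shorter period.

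The direction of the error cannot be known in advance. An arm may heal ulcers sooner and be caught up by the others, or it may give a lasting advantage. The two cases can look identical at 3 months and have very different cost-utility over a year.

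**Working it through.** The article states no QALY figure, so there is nothing to reproduce. The check is of the definition, followed by an illustration of what the cut-off does.

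**Coverage.** SF-12 times in years are 0, 0.25, 0.5 and 1.0 (Table 1). The 3-month area uses 2 of 4 assessments and 0.25/1.00 = 25% of follow-up. With utility at its maximum of 1 throughout, the most a patient can accrue is 0.25 QALY at 3 months and 1.00 at 12 months.

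**Patients still unhealed at 3 months.** Background cites healing with compression of 40–70% at three months, depending on ulcer size, which leaves 30–60% unhealed. Sample size takes 44% for compression plus special dressings. On that figure 1 − 0.44 = 56% of that one arm is unhealed. It is a historical rate for one arm and does not describe the whole trial. Either figure shows that a substantial group is still due treatment when the QALY stops.

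**Effect on the QALY difference.** Assume equal baseline utility and a between-arm difference d reached linearly at 3 months. By the trapezoidal rule the gain to 3 months is

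0.5 × d × 0.25 = 0.125d.

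The gain to 12 months adds the area from 0.25 to 1.0 year, which depends on the later course:

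| Assumed course after 3 months | Area from 3 to 12 months | Total at 12 months | Ratio to 3-month gain |
|---|---|---|---|
| Gone by 6 months, −d at 12 months | 0.5 × d × 0.25 − 0.5 × d × 0.5 = −0.125d | 0 | 0 |
| Gone by 6 months, then zero | 0.5 × d × 0.25 = 0.125d | 0.25d | 2 |
| Linear fade to zero at 12 months | 0.5 × d × 0.75 = 0.375d | 0.5d | 4 |
| Held to 6 months, zero at 12 months | d × 0.25 + 0.5 × d × 0.5 = 0.5d | 0.625d | 5 |
| Sustained to 12 months | d × 0.75 = 0.75d | 0.875d | 7 |

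For d = 0.05 (assumed), the 3-month gain is 0.00625 QALY, and the 12-month gain lies between 0 and 0.04375. The ratios do not depend on d, but they depend entirely on the assumed course. All five courses give the same 3-month result.

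**The case against.** The strongest defence is that 3 months is a deliberate time point. It is the time of the healing rate in the abstract, of the sample size calculation, of the first secondary outcome and of the initial acupuncture course. A short horizon aligned with it is a choice the investigators may make. That is fair, and it justifies reporting a 3-month result. It does not justify making it the only QALY when the later SF-12 and resource data are already scheduled.

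Four stronger readings are tempting and are not supported.

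- **The area is not a QALY because the SF-12 is not a utility.** The text does take the area straight from the SF-12 curve and names no preference-based index. An unconverted score, say an assumed 40 rising to 45, would give 0.25 × (40 + 45)/2 = 10.6 score-years, which cannot be a QALY. But the same sentence speaks of health utility, SF-12 responses can be converted to one, and a condensed article may leave the conversion to the full protocol. What remains is a need for clearer wording.
- **Most costs fall after 3 months.** This is not shown. Assume a constant healing hazard matching 44% at 3 months, λ = −ln(0.56)/3 = 0.193 per month, with treatment until healing. Expected treatment time is 0.44/λ = 2.28 months by month 3, (1 − 0.56²)/λ = 3.55 by month 6 and (1 − 0.56⁴)/λ = 4.67 by month 12. So about 64% of acupuncture time and 49% of a year's dressing and compression time would fall within the first 3 months. Roughly a third to a half would still be missed.
- **The QALY gain is understated 4- to 7-fold.** That range holds only if some benefit lasts until close to 12 months. Other courses give 2 or 0. If costs are cut at 3 months as well, the cost per QALY need not move by the same factor.
- **A stated research question cannot be answered, or the later SF-12 data are wasted.** The economic questions listed are total cost, cost-effectiveness and opportunity cost; cost-utility is a secondary outcome and a listed analysis. The 6- and 12-month SF-12 data are still used for the quality-of-life outcome.

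**Conclusion.** The point holds as a defect of horizon. The article fixes the QALY at 3 months, which is one quarter of follow-up and half of the SF-12 assessments, while treatment, resource recording and re-treatment of recurrence continue. Under the assumed courses, the 12-month QALY difference is between 0 and 7 times the 3-month one, so the 3-month figure cannot tell lasting benefit from earlier healing that the other arms catch up with.

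The multiples rest on equal baselines, a linear rise to 3 months and assumed later courses; none of these comes from the documents. The finding itself does not depend on them, because it follows from the stated schedule. Whether costs and QALYs would actually cover different periods is open, since the article sets no cost horizon.

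The change is worth making but limited in reach. It concerns one secondary economic outcome. The primary healing analysis and the quality-of-life outcome at 3, 6 and 12 months are unaffected.

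**What to change.** Restate the cost-utility rule along these lines:

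1. Compute each patient's QALYs as the area from T0 to T3 (12 months), using all four SF-12 assessments.
2. Adjust the between-arm comparison for baseline utility. The illustration assumed equal baselines, and five clinics per arm cannot guarantee that.
3. Count costs over the same 12 months.
4. Keep the 3-month result as a sensitivity horizon, with costs also limited to 3 months.
5. Say that the area is taken under a preference-based utility derived from the SF-12 responses, and name the index and value set. This clarifies the wording and does not correct a proven error.

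The cost is a change of analysis text. All four SF-12 assessments are already scheduled, and so is resource recording during treatment after 3 months. Item-level SF-12 responses must be kept so that the utility can be derived. The small downside is more missing SF-12 data at 12 months than at 3, and the 3-month sensitivity result helps the reader to judge its influence.

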##### Opportunity cost

this will include the sum of the outputs from the activities potentially left undone as a result of providing a given treatment, rather than a possible alternative, together with the potential financial cost of the resources employed. Using the ABC method, the resources imputed to each patient will be distributed in a multidisciplinary table based on a modular "counter"-type framework for each case, in order to apply the analytical model and to obtain the SF-12 curve showing the variation in health-related quality of life and the potential cost savings for the Public Healthcare System.

#### Covariables

The covariables recorded will be the patient's age, sex, educational level, occupation, income, weight (kg), height (cm), mobility, systolic arterial pressure, diastolic arterial pressure, arm/ankle index and ankle diameter (cm), the duration of the active ulcer (weeks), the location of the ulcer (if more than one ulcer is present, stating the location of the largest one, which is taken as the reference ulcer), whether the ulcer is unilateral or bilateral, the number of ulcers on the leg(s), whether the ulcer is new or recurrent (in the latter case, recording the time since the first appearance, in years and months), the signs of granulation at the base of the ulcer, the signs of epithelialization at the edges of the ulcer, the presence of fibrinous and/or necrotic tissue, the presence of lipodermatosclerosis, and the presence of infection. Other variables recorded will include dependence on tobacco, alcohol or other psychoactive substances, the presence of diabetes mellitus, the results of a nutritional study (haemogram and biochemical tests: albumin, prealbumin, transferrin and proteinogram), the time elapsed until recurrence occurs (weeks), compliance with hygiene-posture recommendations, self care, and the assistance or otherwise of non-professional carers. In addition, a record will be kept of all medication taken (corticoids, immunosuppressors, anticoagulants, etc.) and information about possible cultures of the ulcer exudate.

### Data handling

The data on the variables of interest will be recorded on a purpose-designed form to be completed by each researcher at each clinic. This information will be entered into a database for subsequent statistical analysis.

### Data collection

The routine follow-up evaluation, to be made following cleansing session, will be performed by the nursing staff responsible. The baseline evaluation (T0), that of the results at 3 months (T1), and the follow-up evaluations at 6 and 12 months (T2 and T3) will be carried out by the healthcare personnel responsible for the treatment programme (and who will be blinded with respect to the group to which each patient is assigned).

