#### Randomization and blinding procedure

a list of random numbers will be created, using statistical software, to which the researchers involved in the study will not have access. This list will be applied to the list of participating Clinics until the clusters for each group are obtained. Three types of cluster will be used, according to the treatment for the venous leg ulcer provided at the Clinic (**A: **compression therapy plus simple, low-adherence dressings and acupuncture; **B: **compression therapy plus special dressings; **C: **compression therapy plus simple, low-adherence dressings). Before beginning, the list of Clinics will be randomly ordered, by drawing lots blindly, with no repetitions, from a bag containing the names of all the Clinics taking part. None of those participating in this process will belong to the research group, and none of them will play any further part in the study.

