### Sample size

The sample size has been calculated following the parameters of Campbell et al. [41], on the basis of historical data [18]. The success rate for complete healing of venous leg ulcers at 3 months, with compression bandaging plus special dressings, is 44%. With an alpha (significance) level of 0.05 and a power of detection of differences of 80%, assuming a two-tailed approach, the total sample size needed will be 375 patients, in order to detect differences of 15% between the groups, as regards the rate of complete healing of venous leg ulcers at 3 months. This calculation assumes a possible dropout rate of 5% and an intra-cluster coefficient of correlation of 0.05 (according to the expected variance of the response within a single cluster). There will be 15 clusters (Primary Healthcare Clinics) and so each Clinic will need to recruit 25 subjects. Therefore, 3 treatment arms will be formed, with 125 patients in each (with 5 Clinics per arm).

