### Measurements (measurement times)

#### Baseline evaluation basal (T0)

▪ The data obtained in the examination made prior to beginning treatment will include personal and sociodemographic characteristics, background and case history, ankle/arm index, nutritional status, previous treatment received, results of the ulcer exudate culture, the dimensions of the ulcer and observations regarding its condition, location and duration in an active state, as well as about the patient's health-related quality of life.

▪ Follow up. At each visit, the nurse applying the treatment will record the macroscopic status of the ulcer, any adverse events that may have occurred, the time employed in providing the treatment, the location of the treatment (clinic/home) and the name of the person performing it. If total healing of the ulcer is detected during a routine examination, the treatment programme official at the relevant Clinic should be informed. For the patients in Group A, a record should also be kept of the data concerning the acupuncture session (the number and location of local points).

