### Data analysis

The data analysis will be carried out by personnel blinded to the treatment groups, and for two types of populations: (1) intention to treat (ITT), with all the patients randomized; (2) per protocol (PP), including only the patients with no more than slight variances from the protocol.

The baseline variables for the different groups will be compared, to test the homogeneity produced by random allocation, in terms of differences of the means and of proportions, and the only differences taken into consideration in this comparison will be those that are clinically relevant for subsequent analysis. The magnitude of the difference in any imbalance produced by the random allocation to groups will be evaluated by using ratios of the means, or medians, or proportions, bearing in mind whether the level of analysis is per cluster or per individual.

The final analysis will be carried out as a univariate survival analysis (using the Kaplan-Meyer method and the log-rank-test for inter-group comparison). The hazard ratios for each treatment will be calculated, together with the corresponding NNTs, calculating a 95% confidence interval, using Cox's proportional risk regression model. The assumption of proportionality will be assessed from the interaction between the time elapsed until success (total healing) and treatment group, and will be tested graphically by observing the parallelism in the log-log curves. A multilevel analysis will be carried out to adjust for possible unbalanced variables in the baseline analysis, taking the patients as level 1 and the Primary Healthcare Clinics as level 2. The interactions between clinic and treatment group will be examined, as will the possible variability in the intercept. The level of significance will be set at p < 0.05, for all the tests made. Cost-effectiveness, cost-utility and opportunity cost analyses will be made.

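### The T0–T3 assessors are described as blinded, but they run the treatment programme at clinics that each deliver only one arm

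*Protocol article*

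**What the plan says.** Under Data collection, the routine evaluation after each cleansing session belongs to the treating nurses. The evaluations at T0, T1, T2 and T3 belong to the staff in charge of the treatment programme, "and who will be blinded with respect to the group to which each patient is assigned".

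Four other places in the protocol article bear on that sentence:

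- **Randomization and blinding procedure:** "Three types of cluster will be used, according to the treatment for the venous leg ulcer provided at the Clinic". The Design section calls the trial open-label, with clinics as the randomised clusters.
- **Sample size:** 15 clinics, 25 patients per clinic, 5 clinics and 125 patients per arm.
- **Acupuncture (Study Group A):** nurses at the clinics give all treatment, "coordinated by the treatment programme head in each case".
- **Baseline evaluation (T0), follow-up item:** when the nurse sees total healing at a routine visit, "the treatment programme official at the relevant Clinic should be informed".

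The primary outcome is time to complete epithelialisation of all venous ulcers. Table 1 has the date of complete healing recorded at the weekly treatment visits as well as at T1, T2 and T3. Data analysis says that the analysts are blinded, and defines one analysis population as "intention to treat (ITT), with all the patients randomized".

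**The concern.** Blinded outcome assessment is the main protection an open-label trial can offer when its endpoint is a clinical judgement. Whether every ulcer has fully epithelialised, and in which week that happened, is such a judgement. A reader of the Data collection section would take it that this protection is in place.

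If the assessors know the arm, expectation can influence both whether healing is declared and when. Both feed directly into the Kaplan-Meier, log-rank and Cox analyses. The protocol would then be claiming a safeguard that its own organisation rules out, and the published results would be read with more confidence than they deserve.

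**Working it through.** The plan gives no figure for this point, so the check is mainly to set its statements side by side.

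**Step 1. Does knowing the clinic reveal the arm?** From Sample size: 15 clinics / 3 arms = 5 clinics per arm; 5 × 25 = 125 patients per arm; 15 × 25 = 375 in total. Treatment is a property of the clinic, so the arm does not vary within a clinic. Knowing one clinic's allocation reveals the group of all 25 of its patients.

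**Step 2. Do the T0–T3 assessors know the clinic's arm?** Data collection describes them as in charge of the treatment programme. The acupuncture section has the programme head coordinating the nurses who deliver treatment. The T0 section places the programme official at the patient's clinic. I read these three descriptions as one role, which is the natural reading. Someone who coordinates treatment at a clinic delivering a single arm knows what that treatment is. Nothing in the article describes an assessor from outside the clinic, masked tracings or central adjudication.

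**Step 3. Would true blinding at T1–T3 be enough for the primary outcome?** No. Table 1 has the healing date entered at weekly treatment, and Data collection and the T0 section give those visits to the treating nurse. No blinding is claimed for that nurse, and none is possible. The T0–T3 sentence covers only part of how the primary outcome is ascertained.

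**Step 4. Does the planned analysis remove the problem?** Blinding the analysts does not change data recorded by people who know the arm. The multilevel model adjusts for unbalanced baseline variables and allows for clinic-level variation. A tendency to call healing earlier or more readily throughout one arm is neither of these. Because arm is constant within a clinic, such a tendency cannot be separated from the treatment effect.

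**Step 5. Illustrative size.** The documents give no misclassification rate, so the rates here are assumptions. Sample size gives 44% healed at 3 months with compression plus special dressings, leaving 1 − 0.44 = 0.56 unhealed. If a fraction *m* of these were called healed in one arm only, the apparent difference would shift by 0.56 × *m*:

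| Assumed *m* | Shift | Share of the 15-point target |
|---|---|---|
| 5% | 0.56 × 0.05 = 2.8 points | 2.8 / 15 = 19% |
| 10% | 0.56 × 0.10 = 5.6 points | 5.6 / 15 = 37% |

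This concerns healing at 3 months, a secondary outcome, and starts from the figure for one arm. It shows only that a modest error rate would not be negligible. It does not estimate the effect on time to healing.

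**The case against.** The strongest reply is that the trial is openly declared as open-label, the Discussion accepts that acupuncture cannot be double-blinded, and a condensed article need not describe every assessment safeguard. The first two points are true but concern patients and therapists. None of the three limitations in the Discussion mentions assessors who know the arm. The third point would answer a complaint of missing detail, but this is a positive statement that conflicts with other statements in the same article.

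A reader might also infer that enrolment and consent were carried out by staff who knew the arm, so that selection bias is established. The documents do not support that. They do not say who identifies or consents patients, or when a clinic's arm becomes known to those who recruit. Given recruitment at the treating clinic it is a plausible risk, but not a documented fact.

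Nor can such selection be called beyond repair by analysis, or easily as large as the target effect. Area and duration of the main ulcer are recorded at baseline, and Data analysis plans adjustment for unbalanced baseline variables, although unmeasured factors would remain. The Background gives 3-month healing of 40–70% depending on ulcer size, a 30-point range. A 15-point shift is half of that range: 0.15 / 0.30 = 50% of an arm's patients would have to move from the worst-healing to the best-healing size. That is a large shift.

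Finally, masking by exchange of assessors may be incomplete. This stands, and is reflected in the fix.

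**Conclusion.** The contradiction holds. As the roles are described, the T0–T3 assessors cannot be blind to group. This applies to every scheduled evaluation at all 15 clinics, and so to all 375 planned patients. In addition, the weekly healing date comes from an unblinded nurse. Ascertainment of the primary outcome is therefore open to detection bias that the planned analysis does not remove.

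The conclusion rests on reading the programme personnel, head and official as one role based at the clinic. It does not depend on the illustrative error rates. Neither the direction nor the size of any bias can be derived from the documents, and nothing in them shows that bias has occurred.

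The definition of the intention-to-treat population is a minor, separate point. It refers to randomised patients when only clinics are randomised. No consequence for the results follows from the documents.

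**What to change.** Choose one of two routes.

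1. **Wording only.** Remove the blinding claim from Data collection, and add unblinded outcome assessment to the limitations in the Discussion. This costs nothing beyond the edit.
2. **Make the claim partly true, where feasible.** Existing programme heads carry out T1–T3, and confirm any healing reported by a nurse, at a clinic other than their own. They are not told that clinic's arm, and they examine the leg after bandage removal and before any needling. State whether the nurse's date or the confirmation date enters the survival analysis, with the same rule in all arms, because a confirmation visit can shift the date.

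The second route needs some travel within one health district but no extra assessors. Masking may be partial: the heads share a training course and standardisation meetings and may learn each other's allocations, and patients may reveal their treatment. Confirmation is also still triggered by an unblinded nurse. The text should therefore describe the masking as attempted, not assured.

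Under either route, reword the intention-to-treat population as all enrolled patients analysed by the arm assigned to their clinic.
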